### Data collection

Participant data will be entered by the PI and their delegated nominees into the secure, trial-specific Clinical Data Management System (CDMS):Sealed Envelope’s Red Pill database.

The storage of personal data will be treated as confidential and stored in accordance with the Data Protection Act 2018 and General Data Protection Regulation. Access is limited to authorised users at site and Newcastle University.

Users are assigned role-based permissions specific to their site and study role. Patient identification will be through a unique participant ID, allocated at screening. These IDs will specify hub, site, and individual patient and will be provided sequentially at each site.

Participants will be completing questionnaires for this trial on paper forms at baseline and 6 months. These will be transcribed by the site staff onto the database, and the paper originals will remain at the site. Validations will be built into the Red Pill database, while additional manual validations will also be made to promote data quality. Data management processes are described in the data management plan.

All participants will be given a voucher to the value of £20 for completing the baseline visit. To encourage retention, further £20 vouchers will be given when they complete the 6- and 12-month follow-ups. For those participants who fail to attend the 6-month or 12-month follow-up visit, a member of the site research team will attempt to contact them via telephone or SMS message and establish self-reported smoking status and any adverse events. The option of remote collection through posting out the carbon monoxide monitor will be made available for those who cannot attend in person.

The study data collected are outlined in the Schedule of Events (Table 2). Details of each study measure are given in Additional file 1.

**Table 2 Tab2:** Schedule of events

**Procedures**	**Screening**	***Baseline*** ***(Part 1)***	**Day 7*** (+3 days)	**Day 21**^**$**^ (± 2 days)	**Day 28** (+5 days)	**6 months**^**@**^	**12 months**^**@**^
Informed consent	**X**						
BPE (if not done in previous 3 months)	**X**						
Eligibility assessment	**X**						
Randomisation		***X*** *No more than 3 days before intervention & ordering product*					
Demographics		***X***					
Medical/smoking history (# self-reported smoking status, including type and amount)		***X***				**#**	**#**
Number of teeth (this can be taken from recent BPE)		***X***				**X**	
Expired air carbon monoxide						**X**	**X**
Fagerstrom Test for Nicotine Dependence (FTND)		***X***				**X**	
Mood and Physical Symptoms Scale (MPSS)		***X***				**X**	
Oral Health Quality of Life Assessment (OHQoL-UK)		***X***				**X**	
Health service utilisation questionnaire		***X***				**X**	
AEs and SAEs will be recorded					**X**	**X**	**X**
Concomitant medications (used for AEs)					**X**	**X**	**X**
Behavioural intervention		***X****					
Ordering of trial products		***X**** *Within 48 hours of delivering behavioural intervention*		**X**^**$**^			
Confirmation of receipt of trial products			**X***		**X**^**$**^		
Contingent valuation study						**X**	
Gift Voucher		***X***				**X**	**X**

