#### Randomisation

Following completion of informed consent and confirmation of eligibility, participants will be randomised to receive VBA, NRT, or EC starter kit, in a 1:2:2 ratio using random permuted blocks within strata. Randomisation will be stratified by research hub/region (up to 12 levels) and by baseline periodontal status (3 levels: (i) all sextants BPE code ≤ 2, (ii) 1–3 sextants with BPE code 3 or 4, (iii) ≥ 4 sextants with BPE code 3 or 4).

Randomisation will be performed by a member of trained site staff using the Sealed Envelope™ system (a secure, central, 24h web-based randomisation system which generates the allocation sequence with concealed allocation) [18].

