#### Nicotine Replacement Therapy (NRT)

Participants randomised to the NRT group will be offered standard NRT. A trained dental professional will provide a single-visit behavioural support intervention, including the offer of NRT. Arrangements will be made for the supply of a 12-week course of combination NRT (nicotine patch plus faster-acting form such as chewing gum or lozenge), in line with current recommendations [21]. Stocks of NRT will be kept centrally at Newcastle Specials Pharmacy Production Unit (PPU) and not at each site. Each site is provided with demonstration versions of each product, and the dental professional will select the most appropriate products and strengths in consultation with the participant. These will be ordered by the site, prepared by the Newcastle Specials PPU and dispatched to each participant’s home via secure next day delivery or to the local dental practice for collection. Initially, a 4-week supply will be provided. During the third week, the dental professional will contact the participant via telephone or SMS text message to check on their status, and if required (e.g. they have quit or are still attempting to quit and need more supplies), they will order the further eight-week supply of NRT to be delivered to the patient’s home or dental practice. Participants are also provided with an NRT-specific PIS.

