### Blinding

Prior to randomisation, participants will be blinded to the purpose of the trial and will not be aware of the treatment interventions being offered. The trial will be described in terms of different packages of advice that the dental team can offer rather than describing the interventions in detail (VBA, NRT, EC). Prior to randomisation, the participants will also be unaware that the specific aim of the trial is smoking cessation.

This is a common approach in research studies where some of the interventions are light touch, such as the brief intervention (control group) in this trial. This is done because by explaining the interventions in the PIS, the dental professional has effectively delivered the control brief intervention. Similar approaches have been used in a range of studies [33–35], including a recent smoking cessation study [36]. The PIS will detail that if any ‘medication or other devices’ are offered by the dental professional, the participant can decide not to use these, but if they do, any side effects, benefits, and risks will be discussed by the dental professional to inform the participant’s decision. Participants will receive a randomisation group-specific PIS following randomisation.

For the primary outcome (biochemically verified smoking abstinence at 6 months), assessors will not be blinded to participant allocation or smoking status, but an objective measure will be taken to verify self-reported tobacco abstinence (eCO). For the key secondary outcome (percentage of periodontal sites at 6 months with PPD ≥ 5 mm), the outcome assessors will be blinded to participant allocation and smoking status. Participants will be asked not to disclose their smoking status or methods of smoking cessation to the blinded outcome assessor. There are three trial statisticians: two senior statisticians and a trial statistician. One senior statistician will remain blind to treatment allocation until the end of trial database lock. The remaining two statisticians will not be blinded to treatment allocation.

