***Periodontitis sub-study – Biological Sample collection***							
Sub gingival dental plaque		***X***^***P***^				**X**^Q^	
Buccal brush biopsy		***X***^***P***^				**X**^Q^	
Unstimulated saliva (exploratory data collection in selected sites only)		***X***^***P***^				**X**^Q^	
Calculus sample (exploratory data collection in selected sites only)		***X***^***P***^				**X**^Q^	

**= if randomised to NRT or EC $=If randomised to NRT group only*

^@^* =The follow-up visits are scheduled around the usual 6 monthly recall visits that would be recommended for someone with a risk factor such as tobacco smoking. Ideally this should fall 6 and 12 months from the baseline visit, but no specific visit timing parameters are defined*

^P^*=Baseline: before (maximum of 28 days prior) or on the day of delivery of the intervention*

^Q^*= on the same day as, or a maximum of 28 days after, the 6-month follow-up visit conducted by the primary care team*

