#### Analysis of the primary outcome

The primary outcome of biochemically verified smoking abstinence at 6 months will be analysed using mixed-effects logistic regression adjusted for the stratification factors, research hub/region (random effect), and baseline periodontal status (fixed effect). Average marginal effects between randomisation groups will be calculated from each model to estimate the risk differences at 6 months (EC-VBA, NRT-VBA, EC-NRT). Any participants with missing smoking abstinence data will be regarded as still smoking [41].

A tipping point analysis will be conducted to assess the sensitivity of the assumption that if abstinence is not verified, the participant is still smoking. Details will be given in the pre-specified Statistical Analysis Plan (SAP).

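### An objective eCO does not protect the step of obtaining a reading: with missing scored as smoking, unblinded follow-up of non-attenders and an optional posted monitor leave verification open to differing by arm

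*Protocol article*

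**What the plan says.** Under Blinding, the article states that for the primary outcome "assessors will not be blinded to participant allocation or smoking status, but an objective measure will be taken to verify self-reported tobacco abstinence (eCO"). Under Randomisation, "Randomisation will be performed by a member of trained site staff", so the site knows the allocation from the start.

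Under Data collection, when a participant misses the 6- or 12-month visit, "a member of the site research team will attempt to contact them via telephone or SMS message and establish self-reported smoking status". The same paragraph adds: "The option of remote collection through posting out the carbon monoxide monitor will be made available for those who cannot attend in person". Neither sentence distinguishes between arms, and neither ties the monitor to a reported quit.

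Under Analysis of the primary outcome: "Any participants with missing smoking abstinence data will be regarded as still smoking". A tipping point analysis of that rule is planned, with details left to the SAP.

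The schedule of events (Table 2) and the NRT section set different contact before 6 months. The Day 7 receipt check applies "if randomised to NRT or EC". For NRT only, "During the third week, the dental professional will contact the participant via telephone or SMS text message to check on their status", followed by a Day 28 receipt check. Adverse event recording at Day 28 carries no arm marker and reads as common to all.

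**The concern.** An eCO reading guards against one error: a smoker being recorded as abstinent. It does nothing for the opposite error, a true quitter who is never measured. Under the missing-equals-smoking rule that quitter is recorded as a smoker. Obtaining a reading is therefore part of the outcome, and the stated justification for unblinded assessment does not reach that part.

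That step lies with site staff who know the allocation. The stated aim of their call is self-reported status, which cannot by itself produce a verified quit. Only a later visit or a posted monitor can do that. Sites will also have had more scheduled contact with NRT and EC participants than with VBA participants. If this made quitters in the active arms more likely to yield a reading, part of the observed difference from VBA would be a difference in ascertainment.

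**Working it through.** **Reproducing the plan's figure.** Inputs from Sample size: 6% v 13%, one-sided 2.5%, 85% power, 1:2:2 allocation. The pooled two-proportion formula without continuity correction gives 243 for VBA, hence 243 + 486 + 486 = 1215, with power 85.1%. The stated sample size is reproduced and is not in dispute.

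**Scheduled contacts between baseline and 6 months (Table 2).**
- VBA: Day 28, one contact.
- EC: Days 7 and 28, two.
- NRT: Days 7, 21 and 28, three.

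**Model for unequal verification.** Let q be the true abstinence rate, equal in both arms (no true effect), and v the probability that a true quitter yields an eCO reading. With every unmeasured quitter scored as a smoker and no smoker passing as abstinent, the observed rate is q × v. The article gives no values of v, so those below are assumptions.

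With p1 = q × v(VBA), n1 = 243, p2 = q × v(active), n2 = 486 and pooled rate p = (243·p1 + 486·p2)/729:

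- SE0 = √[p(1−p)(1/243 + 1/486)]
- SE1 = √[p1(1−p1)/243 + p2(1−p2)/486]
- Rejection probability = Φ[(p2 − p1 − 1.96·SE0)/SE1]

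| q | v, VBA v active | Observed rates | Spurious difference | One-sided 2.5% rejection |
|---|---|---|---|---|
| 6% | 70% v 70% | 4.2% v 4.2% | 0 | 2.5% |
| 6% | 70% v 75% | 4.2% v 4.5% | 0.3 points | 3.6% |
| 6% | 70% v 80% | 4.2% v 4.8% | 0.6 points | 5.2% |
| 10% | 70% v 70% | 7.0% v 7.0% | 0 | 2.5% |
| 10% | 70% v 75% | 7.0% v 7.5% | 0.5 points | 4.1% |
| 10% | 70% v 80% | 7.0% v 8.0% | 1.0 point | 6.5% |

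Worked line (q = 10%, 70% v 80%): p = 0.0767, SE0 = 0.0209, SE1 = 0.0205; (0.010 − 1.96 × 0.0209)/0.0205 = −1.51, and Φ(−1.51) ≈ 0.065. Exact binomial enumeration for the two 10-point rows gives 4.9% (q = 6%) and 6.2% (q = 10%), so the inflation is not an artefact of the normal approximation. The z-test stands in for the planned mixed-effects logistic model.

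**EC v NRT.** NRT has the extra contact, so a gap would most plausibly favour NRT, while the planned test is one-sided for EC superior to NRT. With q = 10%, verification 80% (EC) v 85% (NRT) and 486 per arm, the observed rates are 8.0% v 8.5%. Rejection is about 2.7% at nominal 5% and 1.2% at nominal 2.5%. Both are below nominal, so the cost is power.

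**The case against.** The strongest reply is that no passage says chasing will be unequal. The follow-up paragraph is arm-neutral: the same call and the same postal option apply to anyone who does not attend. A reader might infer that VBA quitters will go unverified while EC quitters are posted monitors, or that all three hypotheses are tilted towards a false positive. The documents support neither. The first is a possibility that the wording leaves open. The second fails for EC v NRT, as shown in the working.

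The contact imbalance is also small and early. EC exceeds VBA by one delivery check, and nothing in the article links contact in the first month to obtaining a reading about five months later. The 6-month visit follows usual recall in every arm, the £20 follow-up voucher is the same for all, participants are not told of the other interventions, and the Trial Management Group monitors data collection rates centrally. The number and timing of contact attempts may well be set in the full protocol or a site manual, so their absence from an article is no fault.

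All of this stands, and it makes the risk conditional and probably modest. It does not answer the narrower point: the article offers objectivity of the reading as its answer to unblinding, and that answer does not cover whether a reading exists. The tipping point analysis can show how much imbalance would overturn the result, but it neither equalises verification nor recovers readings that were never taken.

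**Conclusion.** The point holds as a conditional weakness with an inexpensive remedy. As written, a non-attending quitter can be reached, report abstinence and still be scored as a smoker, because the posted monitor is an option for those unable to attend and does not follow automatically from a reported quit. Staff making the contact know the allocation, and earlier contact differs by arm.

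If verification of quitters favoured an active arm, with no true effect and 6% to 10% true abstinence, an assumed 5-point gap would create a difference of 0.3 to 0.5 points from VBA and a 10-point gap one of 0.6 to 1.0 point. Both are small against the 7-point minimal clinically important difference, but the one-sided 2.5% rejection rate would rise to about 3.6% to 4.1% and about 5.2% to 6.5% respectively. With equal verification there is no inflation. The gaps are assumptions, and the documents do not show that any gap will arise. For EC v NRT, a bias towards NRT would lower the chance of rejection.

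**What to change.** In Data collection, replace the optional postal route for those unable to attend with a rule, identical in every arm, that each non-attender who reports abstinence is sent a CO monitor. With the results, report by arm the share of self-reported abstainers who have an eCO reading, so that readers can see whether verification was balanced.

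The rule equalises the offer of verification. It cannot ensure that monitors are used, and it does not help participants who are never reached, so the missing-equals-smoking rule and the tipping point analysis stay as planned. Intervention contacts are untouched.

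The cost is postage and handling for some additional monitors, by a route that the trial already has, and a change of wording.

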***The following assessments are for the Periodontitis sub-study ONLY—collected by the regional blinded hub assessors.***							
PPD (Probing Pocket Depth)		***X***^***P***^				**X**^Q^	
GI (Gingival Index [Lobene Modified Gingival Index])		***X***^***P***^				**X**^**Q**^	
PI (Plaque Index [Silness and Loe plaque index])		***X***^***P***^				**X**^Q^	
Gingival recession		***X***^***P***^				**X**^Q^	
BOP (Bleeding on Probing)		***X***^***P***^				**X**^Q^	
CODS- Clinical Oral Dryness Score		***X***^***P***^				**X**^Q^	
Collection of periodontal therapy details						**X**^Q^	
***Periodontitis sub-study – Biological Sample collection***							
Sub gingival dental plaque		***X***^***P***^				**X**^Q^	
Buccal brush biopsy		***X***^***P***^				**X**^Q^	
Unstimulated saliva (exploratory data collection in selected sites only)		***X***^***P***^				**X**^Q^	
Calculus sample (exploratory data collection in selected sites only)		***X***^***P***^				**X**^Q^	

**= if randomised to NRT or EC $=If randomised to NRT group only*

^@^* =The follow-up visits are scheduled around the usual 6 monthly recall visits that would be recommended for someone with a risk factor such as tobacco smoking. Ideally this should fall 6 and 12 months from the baseline visit, but no specific visit timing parameters are defined*

^P^*=Baseline: before (maximum of 28 days prior) or on the day of delivery of the intervention*

^Q^*= on the same day as, or a maximum of 28 days after, the 6-month follow-up visit conducted by the primary care team*

### Periodontal sub-study

Additional assessments will be conducted at baseline and 6-month visits for the participants in the periodontal sub-study. These will be conducted by the regional hub assessors, who are blinded to the participant’s trial randomisation group and smoking status. Training sessions were held for the examiners (dentist, dental therapist or dental hygienist) and dental nurses from each hub before the first patient recruitment, in the form of an in-person training event in the Newcastle Dental Clinical Research Facility. A range of examiner alignment activities were undertaken. Inter-examiner agreement was assessed against a gold standard, at the mouth level, to ensure the reliability of the inputs to the statistical models for the final analyses. Repeat measures were used to assess intra-examiner reliability. Live data were presented during the sessions, and additional training and repeat exercises completed where necessary. If new examiners join the study, they will be required to complete the examiner alignment activities individually.

The assessments that will be conducted by the hub assessors at baseline and 6 months on participants in the periodontal sub-study are listed in the schedule of events (Table 2).

Sub-study participants will receive an additional £20 voucher on completion of baseline and 6-month assessments. Assessors from the hub will visit the participant’s dental practice to perform the assessments, or in some cases the participant may travel to the hub, in which case they will receive a further additional incentive in the form of a £20 gift voucher to cover any travel expenses.

### Sample size

The sample size calculation was based on a test of the superiority of either NRT or EC compared to VBA, for the primary outcome, according to the Bonferroni-based gatekeeping method (Fig. 1) [37]. If at least one of the two hypothesis tests for NRT or EC compared to VBA is rejected, we will test the superiority of EC compared to NRT.

**Fig. 1 Fig1:**
[figure not shown]
Bonferroni-based gate keeping method

Assuming a rate of biochemically verified smoking abstinence at 6 months for VBA of 6% [38, 39] with a minimal clinically important difference (MCID) of 7% [13, 40], 85% power and type 1 error rate of 2.5%, a total of 1215 participants (VBA= 243; NRT/EC = 486) would be required to perform a one-sided test for each hypothesis (NRT vs VBA, EC vs VBA). If both null hypotheses are rejected, we will carry forward a type 1 error rate of 5%, and based on an NRT rate of 11%, we can detect a difference of 7% with 93% power and 6% with 85% power (one-sided test EC vs NRT). If only one null hypothesis is rejected, we will carry forward a type 1 error rate of 2.5% with which we can detect a difference of 7% with 87% power. Note that this is not inflated for attrition in line with standard research practice in this field [41].

Further details of the sample size calculations for the trial are included in Additional file 1.

### Statistical analysis

#### General analysis principles

Analyses will be conducted for available data according to the ITT principle. Results will be presented as the treatment effect with the *p*-values extracted directly from the model. All comparisons will also be presented with 95% confidence intervals [42]. For the primary outcome, statistical significance will be at the level determined by the Bonferroni-based gatekeeping method (Fig. 1). For all other outcomes, we will present the results of the unpowered comparisons with 2-sided *p*-values, where *p*-values < 0.05 will be considered statistically significant.

#### Analysis of the primary outcome

The primary outcome of biochemically verified smoking abstinence at 6 months will be analysed using mixed-effects logistic regression adjusted for the stratification factors, research hub/region (random effect), and baseline periodontal status (fixed effect). Average marginal effects between randomisation groups will be calculated from each model to estimate the risk differences at 6 months (EC-VBA, NRT-VBA, EC-NRT). Any participants with missing smoking abstinence data will be regarded as still smoking [41].

A tipping point analysis will be conducted to assess the sensitivity of the assumption that if abstinence is not verified, the participant is still smoking. Details will be given in the pre-specified Statistical Analysis Plan (SAP).

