#### Analysis of all other secondary outcomes

The binary secondary outcome measures, such as continuous biochemically verified smoking abstinence at 12 months, will be analysed using a mixed-effects logistic regression model. Numerical secondary outcome measures, such as Oral Health Quality of Life Assessment score, will be analysed using a linear mixed-effects regression model. All models will be adjusted as for the primary outcome, with the addition of the adjustment for the baseline of that outcome if available. Details will be given in the pre-specified Statistical Analysis Plan (SAP).

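### The primary abstinence model leaves out baseline nicotine dependence (FTND) and so forgoes a small gain in precision

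*Protocol article*

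**What the plan says.** The section on the primary outcome names the covariates outright: abstinence is "analysed using mixed-effects logistic regression adjusted for the stratification factors, research hub/region (random effect), and baseline periodontal status (fixed effect"). Risk differences for EC-VBA, NRT-VBA and EC-NRT then come from average marginal effects, and participants with missing abstinence data count as smokers. The Randomisation section stratifies by the same two factors, hub/region (up to 12 levels) and periodontal status (3 levels).

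The schedule of events (Table 2) lists the "Fagerstrom Test for Nicotine Dependence (FTND") at baseline and at 6 months, and Other secondary outcomes places it among the measures taken on all participants. For the remaining secondary outcomes, the models are adjusted as for the primary outcome, "with the addition of the adjustment for the baseline of that outcome if available". Baseline FTND would therefore enter only the model for FTND itself.

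The Sample size section allows for no covariate gain. It starts from "Assuming a rate of biochemically verified smoking abstinence at 6 months for VBA of 6"%, "with a minimal clinically important difference (MCID) of 7"% and "85% power and type 1 error rate of 2.5"%, with a "one-sided test for each hypothesis (NRT vs VBA, EC vs VBA").

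**The concern.** Several features of the design make a baseline measure of dependence relevant. Entry is by self-identification as a regular smoker with no threshold on consumption, so nothing narrows the range of dependence at entry. Expired carbon monoxide is deliberately not measured at baseline. No smoking variable is a stratification factor. Neither the design nor the primary analysis therefore accounts for dependence.

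If dependence predicts quitting in this population, two things are lost. One is some precision in the marginal risk difference. The other is protection of the actual estimate against a chance imbalance. The VBA arm has 243 participants and about 0.06 × 243 = 14.6 expected abstainers, and it is shared by both primary comparisons, so an imbalance in that arm would affect both. The question is how much this amounts to.

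**Working it through.** **1. The plan's own figure.** Inputs from the Sample size section: p0 = 0.06, p1 = 0.13, one-sided α = 0.025, power 0.85, ratio k = 2 within each pair. The pooled formula without continuity correction is

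n0 = [z(1−α)·√((1+1/k)·p̄(1−p̄)) + z(power)·√(p0(1−p0) + p1(1−p1)/k)]² / (p1−p0)²

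- p̄ = (0.06 + 2 × 0.13)/3 = 0.1067, so p̄(1−p̄) = 0.0953.
- First term: 1.960 × √(1.5 × 0.0953) = 0.7410.
- Second term: 1.036 × √(0.0564 + 0.05655) = 0.3483.
- n0 = (1.0893/0.07)² = 242.2, rounded up to 243.

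This reproduces "a total of 1215 participants (VBA= 243; NRT/EC = 486"). Power at 243 and 486 is 85.1%.

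**2. Variance of the risk difference without FTND.**

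V = p0(1−p0)/n0 + p1(1−p1)/n1 = 0.0564/243 + 0.1131/486 = 4.648 × 10⁻⁴.

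**3. Variance with FTND.** The documents give no association between FTND and abstinence, so one is assumed: standardised FTND X ~ N(0,1), and an odds ratio of abstinence between 0.83 and 0.50 per SD, with 0.40 as an extreme. Let m0(X) and m1(X) be the logistic abstinence probabilities, with intercepts set so that they average 0.06 and 0.13. For the marginal risk difference from a correct model,

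V_adj = E[m0(1−m0)]/n0 + E[m1(1−m1)]/n1 + Var(m1−m0)/(n0+n1).

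Example at odds ratio 0.50: 0.05471/243 + 0.10700/486 + 0.00140/729 = 4.472 × 10⁻⁴. The ratio to V is 0.962, a reduction of 3.8%.

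**4. Effect on power.** Dividing 243 by the variance ratio and recomputing the pooled power gives:

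| Assumed OR per SD | Variance reduction | Power vs VBA | Worth, out of 1215 |
|---|---|---|---|
| none (as planned) | – | 85.1% | – |
| 0.83 | 0.3% | 85.2% | 3 |
| 0.74 | 0.7% | 85.4% | 8 |
| 0.67 | 1.3% | 85.6% | 15 |
| 0.57 | 2.5% | 86.0% | 30 |
| 0.50 | 3.8% | 86.5% | 46 |
| 0.40 (extreme) | 6.7% | 87.6% | 81 |

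The last column is 1215 × (1 − variance ratio). With an unpooled Wald test the baseline is 90.1% and the gain over 0.83 to 0.50 is no larger (90.2% to 91.2%). For EC vs NRT (11% vs 17%, one-sided 5%, unpooled Wald), power goes from 85.6% to between 85.7% and 87.3%.

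**5. Chance imbalance.** The SE of a standardised baseline difference between 243 and 486 participants is √(1/243 + 1/486) = 0.079 SD, so 95% of imbalances lie within 1.96 × 0.079 = 0.154 SD. The resulting shift in the risk difference is about imbalance × |ln OR| × p̄(1−p̄):

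- OR 0.83: 0.154 × 0.182 × 0.0953 = 0.0027, about 0.3 points.
- OR 0.50: 0.154 × 0.693 × 0.0953 = 0.0102, about 1.0 point.

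The MCID is 7 points.

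**The case against.** The strongest reply is that nothing here is wrong. The model adjusts for exactly the factors used in randomisation, the sample size holds without any covariate gain, and the gain is about one power point or less over most of the assumed range. All of that stands.

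Four stronger readings are tempting, and the documents do not support them.

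- **Bias or inflated type I error.** Omitting a covariate that was not a stratification factor does neither over randomisation. The 0.3 to 1.0 point shift is conditional on an imbalance near its 95% limit, and the confidence interval and α already allow for such variation.
- **Inconsistency with the secondary models.** Those add a baseline value of the same outcome where one exists. Everyone smokes at entry, so abstinence has no informative baseline, and the rule treats 6-month and 12-month abstinence alike.
- **A gain at no cost.** Baseline questionnaires are on paper, so some FTND values may be missing. Table 2 puts randomisation and the FTND in the same baseline column without giving their order.
- **Established prognosis.** The article describes the FTND as a dependence measure for people attending cessation clinics and does not call it prognostic for quitting among dental patients. Nor can a further gain from smoking amount be claimed: Table 2 ties type and amount to the symbol used at 6 and 12 months.

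The SAP, which is not shown, may already hold a supportive FTND-adjusted analysis. The article nevertheless fixes the primary model's covariates, so the suggestion applies to that model as published.

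**Conclusion.** This is an optional improvement to a valid model. Over the assumed odds ratios of 0.83 to 0.50 per SD, adding baseline FTND would reduce the variance by about 0.3% to 4%, add 0.1 to 1.4 points of power against VBA, and protect the estimate from a shift of roughly 0.3 to 1.0 points. These sizes rest on the assumed association, on FTND being roughly normal and linear on the logit scale, and on nearly complete baseline values. A weaker association would leave almost no gain. A secondary merit is that pre-specification forestalls a post hoc argument should dependence turn out unbalanced across arms.

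**What to change.** Before unblinding, pre-specify the following in the analysis plan:

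- Baseline FTND, continuous, as a fixed effect in the 6-month and 12-month abstinence models, alongside hub/region and periodontal status.
- The average marginal risk difference kept as the estimate, so that the target of estimation does not change.
- Single imputation of missing baseline FTND that uses neither arm nor outcome, so that everyone stays in the missing-equals-smoking analysis.
- Confirmation that the FTND is completed before the participant knows the allocation.
- The strata-only model kept as a sensitivity analysis.

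This needs no extra participants, visits or data collection. The cost is one model term, a missing-value rule and a check on the order of baseline procedures.
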